#### Composition of the data monitoring committee, its role, and reporting structure {21a}

DMC will comprise three independent experts, one of whom will be an expert statistician and the trial statistician. Only the trial statistician will attend from the trial management group, although the chief investigator may attend an open session if requested by the DMC. The trial statistician will present a report and summary of the analyses for the DMC as these are required by the DMC. The DMC will meet biannually prior to TSC meetings and report to the TSC. DMC will monitor for quality, futility, and extreme success. The DMC charter may be requested by contacting the chief investigator.

### Adverse event reporting and harms {22}

Adverse events will be reported via case managers. Minor adverse events (e.g. a participant being distressed during a session) are logged by the case manager and reported to the trial manager. Serious adverse events related to the study or within the study setting (e.g. during a meeting between the participant and case managers) are reported immediately to the chief investigator in accordance with good clinical practice guidelines. If necessary, the adverse event is reported to the sponsor and to the Norwegian Board of Health Supervision.

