### Participant timeline {13}

A participant timeline was created according to the SPIRIT guidance and is presented in Fig. 3 [58]. Following admission to the cohort study, baseline measurement will be completed. After baseline measurement, one in three will be randomly selected to be invited to the intervention (see SPIRIT item 16a). If wishing to join the intervention, the participant will be assigned a case manager who will conduct the initial assessment. The case manager will then match the participant to a suitable work placement in collaboration with Manpower. The participant, case manager, and placement supervisor will agree and sign a return to work plan, and the participant will attend a 2-day work familiarisation session prior to the 6-week placement. Self-reported follow-up questionnaires will be completed by all participants 3, 6, and 12 months after baseline.

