### Harms

The frequency and percentage (%) of serious adverse events and adverse events in the trial will be compared between the two treatments using the chi-squared test provided the expected values in the cross-tabulation are greater than 5; otherwise, Fisher’s exact test will be used. Odds ratios and 95% confidence intervals will be reported. Adjusted analyses will not be performed for any harm data. The event type, severity assessment, expectedness, and relatedness to intervention will also be summarised by offer of treatment or cohort only.

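### Adverse events are routed through case managers, whom only intervention accepters have, yet event rates are to be tested between offered and cohort-only groups

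*Protocol article*

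**What the plan says.** Four places in the protocol article bear on this.

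- **Adverse event reporting and harms {22}.** The route is stated in one sentence: "Adverse events will be reported via case managers". Minor events "are logged by the case manager and reported to the trial manager". The reporting duty for serious events is worded as "Serious adverse events related to the study or within the study setting". Both examples given, distress in a session and a meeting with a case manager, belong to the intervention.
- **Participant timeline {13}.** "If wishing to join the intervention, the participant will be assigned a case manager who will conduct the initial assessment". Cohort-only participants, and people who are offered the intervention and decline, therefore have no case manager.
- **Harms (statistical methods).** Frequencies of serious and other adverse events "will be compared between the two treatments using the chi-squared test provided the expected values in the cross-tabulation are greater than 5", with Fisher's exact test otherwise, and odds ratios with 95% confidence intervals. Event characteristics are to be "summarised by offer of treatment or cohort only". "Adjusted analyses will not be performed for any harm data".
- **Outcomes {12}, Table 1 and text.** Table 1 has an adverse events row, with case report forms as the instrument, marked at T1, T2 and T3. It states neither who fills in the forms nor which group they cover. The text listing what follow-up asks of participants mentions care, medication and work, but has no adverse-event item.

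**The concern.** If the named route is the one used, whether an event is recorded depends on whether the person took up the treatment. The between-group test then measures who was being watched as well as who was harmed. The error has a direction: events go unrecorded mainly in the cohort-only group, so the offered group looks worse even when true risks are equal. For events that can arise only in a session, meeting or placement, the cohort-only count is zero because there is no exposure, and a test against that zero says nothing useful.

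At stake is a published odds ratio suggesting harm from an intervention that may be harmless, while real events in the cohort-only group go unseen. This cannot be put right at analysis, because events that were never collected cannot be recovered.

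**Working it through.** **Arm sizes.** The article gives no adverse event figure to reproduce, so its sample size serves only to set the arms. A two-sided 5% test with 80% power, 10% v 30%, three controls per intervention participant and a continuity correction gives 44 + 132 = 176, as stated in Sample size {14}. Inflation: 132/0.8 = 165 cohort-only; 44 × 1.14/0.8 = 62.7, so 63 offered; 165 + 63 = 228, as stated. If one in three of 228 is selected instead, the arms are 76 and 152.

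**Model.** The inputs below are assumptions, because the article gives none of them.

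- r: true event risk, equal in both groups (5%, 10%, 20%)
- a: proportion of those offered who accept (50%, 75%, 100%)
- c: proportion of events captured in people without a case manager (0, 0.5, 1); capture is complete in accepters

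Recorded risk in the offered group = r × [a + (1 − a) × c]. Recorded risk in the cohort-only group = r × c. Decliners stay in the offered group, as the Harms section implies.

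**Events needed for significance when c = 0.** The Fisher p-value for k events against none in 63 v 165 is C(63,k)/C(228,k).

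- k = 2: (63 × 62)/(228 × 227) = 3,906/51,756 = 0.075
- k = 3: (63 × 62 × 61)/(228 × 227 × 226) = 238,266/11,696,856 = 0.020

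Three logged events are enough. With 76 v 152, three against none gives p = 0.036.

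**One cell by hand.** With r = 5%, a = 75% and c = 0, the recorded risk in the offered group is 0.05 × 0.75 = 0.0375. For a binomial count with n = 63, P(0) = 0.090, P(1) = 0.221 and P(2) = 0.267. So P(3 or more) = 1 − 0.578 = 0.42.

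**Full enumeration.** This applies the Harms rule (uncorrected chi-squared if every expected count exceeds 5, otherwise Fisher, two-sided 0.05) to the exact binomial distributions for 63 v 165. Entries are the percentage of trials that reject although true risks are equal.

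| Acceptance | Capture without a case manager | r = 5% | r = 10% | r = 20% |
|---|---|---|---|---|
| 50% | none | 21 | 62 | 96 |
| 75% | none | 42 | 86 | 99.7 |
| 100% | none | 62 | 96 | about 100 |
| 75% | half | 9 | 18 | 34 |
| any | full (equal) | 3.3 | 4.6 | 5.0 |

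With no capture, every rejection is an excess in the offered arm; with half capture, almost every one is. With equal capture the test holds its nominal level. With 76 v 152 and 75% acceptance, no capture gives 55%, 93% and about 100%, and half capture gives 11%, 20% and 37%.

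**The case against.** The best counter-argument is Table 1. Its adverse events row is not limited to one arm, although other rows are limited to those who return to work. Collection at 3, 6 and 12 months also fits trial-wide follow-up better than logging by a case manager whose support is described for a 6-week placement. A journal article may leave form instructions to the full protocol. This stands in part: the row could be a route for everyone, and if it worked equally in both groups the bias would shrink or vanish. But the article does not say so, the section devoted to adverse events names only case managers, and the listed follow-up content has no matching item. The problem is a stated route that does not fit a stated test, not missing detail.

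Second, section {22} leans towards events tied to the study or its setting. Cohort-only participants have no sessions or placements, so a count near zero there may be partly real. This stands. For such events the comparison is uninformative rather than falsely positive, and the calculation above, which assumes equal true risk, does not describe them.

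Third, a reader might infer that cohort-only events will be zero by construction and that the trial will show a false excess. Such a reader might take 57 v 171 at a 10% risk, giving 6/57 v 0/171 and Fisher p = 0.0002. The documents do not support that certainty. The Table 1 row leaves another route open. The example gives every offered person full capture although decliners have no case manager. The article's own inflation also implies 63 v 165.

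Fourth, a reader might infer that the data monitoring committee would be misled. Its stated remit is quality, futility and extreme success, and no harm-based rule is tied to this test. Event type and relatedness will also be summarised by group, which helps a reader interpret the counts.

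**Conclusion.** The point holds: sections {12} (Table 1), {22} and Harms do not fit together and are wrong as written. Following the text, recording of adverse events depends on accepting the intervention. The planned comparison is then expected to be biased towards an apparent excess in the offered arm, or uninformative for events specific to the intervention.

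The size rests on assumed event, acceptance and capture rates. The false rejection rate runs from about a fifth of trials (5% risk, 50% acceptance, no other capture) to nearly all (20% risk, 75% acceptance). Partial capture brings it down to 9–34% at 75% acceptance. With two or fewer logged events against none, the excess would be numerical only. The direction does not depend on these choices as long as capture is poorer without a case manager. The sample size and the primary outcome are not affected.

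**What to change.** Reconcile Table 1, section {22} and the Harms section in one of two ways.

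1. Ask all participants, in both groups and including decliners, the same adverse-event item at 3, 6 and 12 months. State in Table 1 and section {22} who completes it. Limit the between-arm comparison to that source and the patient-registry data already planned for everyone under Cost-effectiveness. Describe case-manager-logged events for the intervention arm only.
2. Drop the between-arm test and odds ratios for case-manager-reported events, and describe those events in the intervention arm.

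The first costs one extra questionnaire item, slight respondent burden and revised wording. The second costs wording only, but gives up any comparative statement on those events. Neither changes the intervention, the sample size or the primary analysis. The first must be in place before follow-up data are collected.

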### Frequency and plans for auditing trial conduct {23}

If the investigators, sponsor, DMC, or TSC become concerned about any aspects of trial conduct, the trial management group or sponsor will evaluate the need to bring in an independent auditor to resolve trial conduct issues.

### Plans for communicating important protocol amendments to relevant parties (e.g. trial participants, ethical committees) {25}

Protocol amendments will be submitted for the Norwegian Centre for Research Data and Regional Ethics Committee approval if required and revised protocols provided to the funder. Substantial modifications will be communicated to all parties by the chief investigator. Minor administrative modifications that will not affect the conduct of the study will be approved in monthly meetings of the trial management group to consider any further action (e.g. notice to the funder, updating ISRCTN registry, and public announcement if necessary).

### Dissemination plans {31a}

We aim to publish the trial report in a high-impact peer-reviewed journal. We will include user representatives as authors to ensure lay summaries and abstracts are accessible and relevant. We will present the results at national and international conferences on pain, work, and health. We will create a lay report for the consumption of participants and all potential users. We will engage users with persistent pain via a bespoke website and dedicated social media channels, which will be regularly updated to promote resource updates, debates, and relevant news articles. We will create a Norwegian-language manual documenting process, fidelity, and results and make this available in addition to an executive summary. Led by a work and health policy expert, we will develop policy briefs specifically for the consumption of policymakers, so findings can be readily used to inform policymaking.

## Discussion

The project addresses the needs of a large vulnerable unemployed group with persistent pain. A deeper understanding of large diagnosis groups comprising musculoskeletal disorders (which accounts for most persistent pain) may make it possible to give such individuals a longer, healthier, and more rewarding working life. Many with persistent pain may appear to have individually complex obstacles to working. However, a novel multidisciplinary approach, featuring matched work placements and case management (tailored for people with pain), may offer a simple, practical, and effective solution. With international collaborative partners, and experts in chronic pain and work and health, the team has previously developed and established the feasibility of this novel intervention in the UK. Strong user involvement has been integrated since the point of design and will continue throughout trial management, dissemination, and all our comprehensive planned impact activities. This will help to ensure that the intervention, trial, and dissemination of results will be relevant, have a meaningful impact, and help to create new pathways to benefit users and the wider society in the case of cost-effectiveness. Known challenges associated with the trials of interventions such as this include participant recruitment, placement provider recruitment, and timing of intervention. In the English feasibility study, the mean time between baseline measurement and the start of work placement was 94.8 days (SD = 35.5). Additionally, placement providers expressed concern over the time and resources needed to onboard a person into a work placement that is part-time for a limited period (e.g. general preparation, introduction to IT systems, data protection training). We aim to address these concerns by using a broad recruitment strategy informed by our feasibility study and Norwegian trials with similar populations and flexibility over adding additional placement providers [13, 76]. Allowing placement providers to provide training and onboarding prior to the 6-week placement may improve the recruitment of placement providers [13]. A defined timeline from baseline measurement to placement is monitored by the trial manager which might aid the timing of the intervention.

### Implications

There are clear pathways for multiple impact vectors from this work. Our study will provide valuable information on the effectiveness and cost-effectiveness of a biopsychosocial intervention that empowers participants to identify their own obstacles to work and provides a safe environment to overcome those obstacles with support. A cost-effective intervention would have several direct societal impacts. Importantly, it will provide a pathway back to work for an experienced group at a time when the percentage of older people outside the workforce has increased and is unsustainable. This will lead to more years of work and more opportunities and create value for the industry. Working longer will not only decrease the period at the end of working life, reducing demand on welfare services, but create synergy through simultaneously improving health and lowering demand on health services. Family and partners often have care duties for those with persistent pain and relationship strains impact quality of life [60, 77]. Improving work participation would thus improve the quality of life not only for people with pain, but also for partners and families through reducing these strains. Participants in our feasibility study commented that the intervention helped them feel more connected and less alone [13]. Thus, the intervention may not only reduce the national social burden of disability, but also facilitate integration and good society.

## Trial status

Protocol version 1.0 (31/01/2023).

Recruitment start date: January 2023 (with pre-pilot recruitment started in September 2022).

Recruitment end date: December 2023.

## Data Availability

Upon study completion, a de-identified dataset will be archived in a data repository. Following completion of the project, de-identified study data may be accessed upon request to the corresponding author.

## Abbreviations

DMC: Data monitoring committee
GDPR: General Data Protection Regulation
KUC: Kristiania University College
NAV: Norwegian Labour and Welfare Administration
OsloMet: Oslo Metropolitan University
RTW: Return to work
RCT: Randomised controlled trial
TSC: Trial steering committee
TSD: Services for sensitive data
UiO: University of Oslo
